#### 17.1.2 Visual Analogue Scale (VAS)

The EQ-5D-5L Visual Analogue Scale (VAS) ranges from 0 to 100.

- Maximum Value: 100, representing the best health you can imagine.
- Minimum Value: 0, representing the worst health you can imagine.

#### 17.2 EORTC-QLQ-CR29

- Sources: [https://drive.google.com/file/d/16j3pr9bEYVBra2tMp6B\\_2QLnxJ85kaDP/view](https://drive.google.com/file/d/16j3pr9bEYVBra2tMp6B_2QLnxJ85kaDP/view)  
<https://www.eortc.org/app/uploads/sites/2/2018/08/Specimen-CR29-English-2.1.pdf>  
<https://www.ncbi.nlm.nih.gov/pmc/articles/PMC6541702/>
- Online calculator: [https://score.awellhealth.com/calculations/eortc\\_qlq\\_cr29](https://score.awellhealth.com/calculations/eortc_qlq_cr29)

The EORTC QLQ-CR29 is a patient-reported outcome measure to evaluate health-related quality of life among colorectal cancer (CRC) patients in research and clinical practice. For the scoring rules see here: [https://drive.google.com/file/d/16j3pr9bEYVBra2tMp6B\\_2QLnxJ85kaDP/view](https://drive.google.com/file/d/16j3pr9bEYVBra2tMp6B_2QLnxJ85kaDP/view) .

The questionnaire includes 29 items, numbered 31 to 59. They are divided into two categories: items about symptoms (gastrointestinal, urinary, pain and others) and items about functions (sexual, body image and others) that are associated with CRC and its treatments. There are separate versions of items 49 to 54 for people with and without stomas, and item 55 is only for patients with a stoma. Items 56 and 57 are for men only, and items 58 and 59 are for women only.

All the QLQ-CR29 questions except one (item 48 requires a yes or no answer) have four possible answers. They are

- Not at all (1)
- A little (2)
- Quite a bit (3)
- Very much (4)

# CARE

Pre-operative intentional weight loss to support post-operative recovery in patients with overweight and colorectal cancer: the CARE feasibility randomised controlled trial. IRAS Project ID: 320173

Those four levels are a Likert scale of four response categories and are linearly converted into a scale from 0 to 100 (ie 0,33,67,100 or 100,67,33,0). Patients are asked to indicate their symptoms during the past week except for the sexuality questions, which ask for the past four weeks.

**Table: EORTC-QLQ-CR29 Functional Scales (0 is bad, 100 is good)**

| Scale                   | Scale name | Number of items | Item #   | Question # | 100 score at      |
|-------------------------|------------|-----------------|----------|------------|-------------------|
| Body_image              | BI         | 3               | 15,16,17 | 45,46,47   | Not at all (1)    |
| Anxiety                 | ANX        | 1               | 13       | 43         | Not at all (1)    |
| Weight                  | WEI        | 1               | 14       | 44         | Not at all (1)    |
| Sexual_interest_(men)   | SEXM       | 1               | 26       | 56         | Very much (4) [1] |
| Sexual_interest_(women) | SEXW       | 1               | 28       | 58         | Very much (4) [1] |

**Table: EORTC-QLQ-CR29 Symptom scales (0 is good, 100 bad)**

| Scale                    | Scale name | Number of items | Item # | Question # | 100 score at  |
|--------------------------|------------|-----------------|--------|------------|---------------|
| Urinary_frequency        | UF         | 2               | 1,2    | 31,32      | Very much (4) |
| Blood_and_mucus_in_stool | BMS        | 2               | 8,9    | 38,39      | Very much (4) |
| Stool_frequency*         | SF         | 2               | 22,23  | 52,53      | Very much (4) |
| Urinary_incontinence     | UI         | 1               | 3      | 33         | Very much (4) |
| Dysuria                  | DY         | 1               | 4      | 34         | Very much (4) |
| Abdominal_pain           | AP         | 1               | 5      | 35         | Very much (4) |
| Buttock_pain             | BP         | 1               | 6      | 36         | Very much (4) |
| Bloating                 | BF         | 1               | 7      | 37         | Very much (4) |
| Dry_mouth                | DM         | 1               | 10     | 40         | Very much (4) |
| Hair_loss                | HL         | 1               | 11     | 41         | Very much (4) |
| Taste                    | TA         | 1               | 12     | 42         | Very much (4) |
| Flatulence*              | FL         | 1               | 19     | 49         | Very much (4) |
| Faecal_incontinence*     | FI         | 1               | 20     | 50         | Very much (4) |
| Sore_skin*               | SS         | 1               | 21     | 51         | Very much (4) |
| Embarrassment*           | EMB        | 1               | 24     | 54         | Very much (4) |
| Stoma_care_problems      | STO        | 1               | 25     | 55         | Very much (4) |
| Impotence                | IMP        | 1               | 27     | 57         | Very much (4) |
| Dyspareunia              | DYS        | 1               | 29     | 59         | Very much (4) |

**Table: EORTC-QLQ-CR29 Questions**

| #  | #  | Code             | Question                                                                        | Levels | Scale      | Scale name               | 100 at         | NB |
|----|----|------------------|---------------------------------------------------------------------------------|--------|------------|--------------------------|----------------|----|
| 31 | 1  | EORTCQLQCR29_Q31 | Did you urinate frequently during the day during the past week?                 | 4      | Symptom    | Urinary frequency        | Very much (4)  |    |
| 32 | 2  | EORTCQLQCR29_Q32 | Did you urinate frequently during the night during the past week?               | 4      | Symptom    | Urinary frequency        | Very much (4)  |    |
| 33 | 3  | EORTCQLQCR29_Q33 | Have you had any unintentional release (leakage) of urine during the past week? | 4      | Symptom    | Urinary incontinence     | Very much (4)  |    |
| 34 | 4  | EORTCQLQCR29_Q34 | Did you have pain when you urinated during the past week?                       | 4      | Symptom    | Dysuria                  | Very much (4)  |    |
| 35 | 5  | EORTCQLQCR29_Q35 | Did you have abdominal pain during the past week?                               | 4      | Symptom    | Abdominal pain           | Very much (4)  |    |
| 36 | 6  | EORTCQLQCR29_Q36 | Did you have pain in your buttocks/anal area/rectum during the past week?       | 4      | Symptom    | Buttock pain             | Very much (4)  |    |
| 37 | 7  | EORTCQLQCR29_Q37 | Did you have a bloated feeling in your abdomen during the past week?            | 4      | Symptom    | Bloating                 | Very much (4)  |    |
| 38 | 8  | EORTCQLQCR29_Q38 | Have you had blood in your stools during the past week??                        | 4      | Symptom    | Blood and mucus in stool | Very much (4)  |    |
| 39 | 9  | EORTCQLQCR29_Q39 | Have you had mucus in your stools during the past week??                        | 4      | Symptom    | Blood and mucus in stool | Very much (4)  |    |
| 40 | 10 | EORTCQLQCR29_Q40 | Did you have a dry mouth during the past week?                                  | 4      | Symptom    | Dry mouth                | Very much (4)  |    |
| 41 | 11 | EORTCQLQCR29_Q41 | Have you lost hair as a result of your treatment during the past week?          | 4      | Symptom    | Hair loss                | Very much (4)  |    |
| 42 | 12 | EORTCQLQCR29_Q42 | Have you had problems with your sense of taste during the past week?            | 4      | Symptom    | Taste                    | Very much (4)  |    |
| 43 | 13 | EORTCQLQCR29_Q43 | Were you worried about your health in the future during the past week?          | 4      | Functional | Anxiety                  | Not at all (1) |    |
| 44 | 14 | EORTCQLQCR29_Q44 | Have you worried about your weight during the past week?                        | 4      | Functional | Weight                   | Not at all (1) |    |

# CARE

Pre-operative intentional weight loss to support post-operative recovery in patients with overweight and colorectal cancer: the CARE feasibility randomised controlled trial. IRAS Project ID: 320173

|    |    |                           |                                                                                                              |   |            |                         |                |     |
|----|----|---------------------------|--------------------------------------------------------------------------------------------------------------|---|------------|-------------------------|----------------|-----|
| 45 | 15 | EORTCQLQCR29_Q45          | Have you felt physically less attractive as a result of your disease or treatment during the past week?      | 4 | Functional | Body Image              | Not at all (1) |     |
| 46 | 16 | EORTCQLQCR29_Q46          | Have you been feeling less feminine/masculine as a result of your disease or treatment during the past week? | 4 | Functional | Body Image              | Not at all (1) |     |
| 47 | 17 | EORTCQLQCR29_Q47          | Have you been dissatisfied with your body during the past week?                                              | 4 | Functional | Body Image              | Not at all (1) |     |
| 48 | 18 | EORTCQLQCR29_Q48          | Do you have a stoma bag (colostomy/ileostomy)?                                                               | 2 | n/a        | n/a                     | Very much (4)  |     |
| 49 | 19 | EORTCQLQCR29_Q49_NO_STOMA | Have you had unintentional release of gas/flatulence from your back passage during the past week?            | 4 | Symptom    | Flatulence*             | Very much (4)  | [1] |
| 49 | 19 | EORTCQLQCR29_Q49_STOMA    | Have you had unintentional release of gas/flatulence from your stoma bag during the past week?               | 4 | Symptom    | Flatulence*             | Very much (4)  | [2] |
| 50 | 20 | EORTCQLQCR29_Q50_NO_STOMA | Have you had leakage of stools from your back passage during the past week?                                  | 4 | Symptom    | Faecal incontinence*    | Very much (4)  | [1] |
| 50 | 20 | EORTCQLQCR29_Q50_STOMA    | Have you had leakage of stools from your stoma bag during the past week?                                     | 4 | Symptom    | Faecal incontinence*    | Very much (4)  | [2] |
| 51 | 21 | EORTCQLQCR29_Q51_NO_STOMA | Have you had sore skin around your anal area during the past week?                                           | 4 | Symptom    | Sore skin*              | Very much (4)  | [1] |
| 51 | 21 | EORTCQLQCR29_Q51_STOMA    | Have you had sore skin around your stoma during the past week?                                               | 4 | Symptom    | Sore skin*              | Very much (4)  | [2] |
| 52 | 22 | EORTCQLQCR29_Q52_NO_STOMA | Did frequent bowel movements occur during the day during the past week?                                      | 4 | Symptom    | Stool frequency*        | Very much (4)  | [1] |
| 52 | 22 | EORTCQLQCR29_Q52_STOMA    | Did frequent bag changes occur during the day during the past week?                                          | 4 | Symptom    | Stool frequency*        | Very much (4)  | [2] |
| 53 | 23 | EORTCQLQCR29_Q53_NO_STOMA | Did frequent bowel movements occur during the night during the past week?                                    | 4 | Symptom    | Stool frequency*        | Very much (4)  | [1] |
| 53 | 23 | EORTCQLQCR29_Q53_STOMA    | Did frequent bag changes occur during the night during the past week?                                        | 4 | Symptom    | Stool frequency*        | Very much (4)  | [2] |
| 54 | 24 | EORTCQLQCR29_Q54_NO_STOMA | Did you feel embarrassed because of your bowel movement during the past week?                                | 4 | Symptom    | Embarrassment*          | Very much (4)  | [1] |
| 54 | 24 | EORTCQLQCR29_Q54_STOMA    | Did you feel embarrassed because of your stoma during the past week?                                         | 4 | Symptom    | Embarrassment*          | Very much (4)  | [2] |
| 55 | 25 | EORTCQLQCR29_Q55_STOMA    | Did you have problems caring for your stoma during the past week?                                            | 4 | Symptom    | Stoma care problems     | Very much (4)  | [2] |
| 56 | 26 | EORTCQLQCR29_Q56          | To what extent were you interested in sex during the past four weeks?                                        | 4 | Functional | Sexual interest (men)   | Very much (4)  | [3] |
| 57 | 27 | EORTCQLQCR29_Q57          | Did you have difficulty getting or maintaining an erection during the past four weeks?                       | 4 | Symptom    | Impotence               | Very much (4)  | [3] |
| 58 | 28 | EORTCQLQCR29_Q58          | To what extent were you interested in sex during the past four weeks?                                        | 4 | Functional | Sexual interest (women) | Very much (4)  | [4] |
| 59 | 29 | EORTCQLQCR29_Q59          | Did you have pain or discomfort during intercourse during the past four weeks?                               | 4 | Symptom    | Dyspareunia             | Very much (4)  | [4] |

[1] Answer this question only when you DO NOT have a stoma bag.

[2] Answer this question only when you have a stoma bag.

[3] For men only.

[4] For women only

## 17.3 HADS

- Sources: <https://www.ncbi.nlm.nih.gov/pmc/articles/PMC5700594>, <https://academic.oup.com/occmed/article/64/5/393/1436876>, <https://score.awellhealth.com/calculations/hads/documentation>
- Online calculator: <https://score.awellhealth.com/calculations/hads>
- Note: HADS is a generated score in the SITU RedCap for this project.

The HADS questionnaire measures hospital anxiety or depression level.

It has fourteen questions divided into two subscales. There are seven questions for one subscale (depression) and seven questions for the other (anxiety). Scoring for each item ranges from zero to

three, with three denoting highest anxiety or depression level. So depression ranges from 0 (good) to 21 (bad), and anxiety ranges from 0 (good) to 21 (bad). A score of more than 8 means considerable symptoms of anxiety or depression.

**Table: items on the questionnaire that relate to anxiety**

| QUESTIONS                                                                   | ANSWERS                                                                                                | SCORE |
|-----------------------------------------------------------------------------|--------------------------------------------------------------------------------------------------------|-------|
| I feel tense or wound up                                                    | Most of the time; A lot of the time; From time to time, occasionally; Not at all                       | 3-0   |
| I get a sort of frightened feeling as if something awful is about to happen | Very definitely and quite badly; Yes, but not too badly; A little, but it doesn't worry me; Not at all | 3-0   |
| Worrying thoughts go through my mind                                        | A great deal of the time; A lot of the time; From time to time, but not too often; Only occasionally   | 3-0   |
| I can sit at ease and feel relaxed                                          | Definitely; Usually; Not often; Not at all                                                             | 0-3   |
| I get a sort of frightened feeling like 'butterflies' in the stomach        | Not at all; occasionally; Quite often; Very often                                                      | 0-3   |
| I feel restless as I have to be on the move                                 | Very much indeed; Quite a lot; Not very much; Not at all                                               | 3-0   |
| I get sudden feelings of panic                                              | Very often indeed; Quite often; Not very often; Not at all                                             | 3-0   |

**Table: items on the questionnaire that relate to depression**

| QUESTIONS                                      | ANSWERS                                                                                                                 | SCORE |
|------------------------------------------------|-------------------------------------------------------------------------------------------------------------------------|-------|
| I still enjoy the things I used to enjoy       | Definitely as much; Not quite so much; Only a little; Hardly at all                                                     | 0-3   |
| I can laugh and see the funny side of things   | As much as I always could; Not quite so much now; Definitely not so much now; Not at all                                | 0-3   |
| I feel cheerful                                | Not at all; Not often; Sometimes; Most of the time                                                                      | 3-0   |
| I feel as if I am slowed down                  | Nearly all the time; Very often; Sometimes; Not at all                                                                  | 3-0   |
| I have lost interest in my appearance          | Definitely; I don't take as much care as I should; I may not take quite as much care ; I take just as much care as ever | 3-0   |
| I look forward with enjoyment to things        | As much as I ever did; Rather less than I used to; Definitely less than I used to; Hardly at all                        | 0-3   |
| I can enjoy a good book or radio or TV program | Often; Sometimes; Not often; Very seldom                                                                                | 0-3   |

**18. APPENDIX: SCREENSHOT OF EORTC-QLQ-CR29 QUESTIONNAIRE**

[figure not shown]

## 19. APPENDIX: SCREENSHOT OF HADS QUESTIONNAIRE

[figure not shown]

## 20. APPENDIX: LINEAR MIXED MODEL THEORY

### 20.1 Linear mixed models: links

See <https://stats.oarc.ucla.edu/other/mult-pkg/introduction-to-linear-mixed-models/>

### 20.2 Linear mixed models: the theory

The formula is:

$$y = xb + zu + e$$

where

| Symbol | Description                                        | Type                    |
|--------|----------------------------------------------------|-------------------------|
| $n_y$  | number of values of the outcome variable           | Scalar                  |
| $n_p$  | number of predictor variables                      | Scalar                  |
| $n_j$  | number of groups                                   | Scalar                  |
| $n_q$  | number of random intercepts per group              | Scalar                  |
| $y$    | outcome variable                                   | $n_y \times 1$ vector   |
| $x$    | predictor variables aka fixed-effects variables,   | $n_y \times n_p$ matrix |
| $b$    | fixed-effects regression coefficients (parameters) | $n_p \times 1$ vector   |
| $z$    | random effects variables                           | $n_y \times n_j$ matrix |
| $u$    | random-effects regression coefficients             | $n_j \times 1$ vector   |
| $e$    | residuals (error)                                  | $n_y \times 1$ vector   |

### 20.3 Linear mixed models: worked example

Consider this scenario:

*Arm ( $J=2$ ) indexed by the  $j$  subscript each see  $n_j$  patients. So our grouping variable is the arm. Each arm sees 36 patients. The total number of patients is the sum of the patients seen by each arm. In our example,  $N=72$ , so 72 patients were seen by two arms. Our outcome is a continuous variable, output weight. Furthermore we have 3 fixed effects predictors, baseline value, timepoint, and stratification variable, plus a fixed intercept and one random intercept ( $q=1$ ) for each of the  $J=2$  arms. For simplicity, we are only going to consider random intercepts. We will let every other effect be fixed for now. The reason we want any random effects is because we expect that output weights within arms may be correlated.*

So the formula is

$$y = xb + zu + e$$

That gives us this table below:

| Symbol | Description                                                                                                                                                                                           | Type              |
|--------|-------------------------------------------------------------------------------------------------------------------------------------------------------------------------------------------------------|-------------------|
| ny     | number of values of the outcome variable                                                                                                                                                              | 72                |
| np     | number of predictor variables                                                                                                                                                                         | 4                 |
| nj     | number of groups                                                                                                                                                                                      | 2                 |
| nq     | number of random intercepts per group                                                                                                                                                                 | 1                 |
| y      | outcome variable                                                                                                                                                                                      | 72 x 1 vector     |
| x      | Four predictor variables aka fixed-effects variables, 
 
Fixed intercept
 
baseline value,
 
timepoint,
 
stratification variable
 
 | 72 x 4 matrix     |
| b      | fixed-effects regression coefficients (parameters)                                                                                                                                                    | 4 x 1 vector      |
| z      | One random effects variable 
 
Random intercept
 
                                                                                                        | 72 x (1x2) matrix |
| u      | random-effects regression coefficients                                                                                                                                                                | 2 x 1 vector      |
| e      | residuals (error)                                                                                                                                                                                     | 72 x 1 vector     |

## 21. APPENDIX: USE OF THE WORD “LINEAR” IN LINEAR MODELS

The word “linear” in “linear models” refers to the parameters, not the variables: it can cope with quadratic equations

- <https://www.quora.com/Why-is-linear-regression-called-linear-if-we-can-use-quadratic-equations-in-our-model-which-gives-a-curved-line>
- <https://www.quora.com/Why-is-it-still-called-linear-regression-even-if-we-choose-a-polynomial-of-a-higher-degree-for-the-hypothesis>

## 22. APPENDIX: LOOKUP TABLE

The type of a variable can be used to deduce the variable distribution - for example a variable measuring strength may have a Gamma distribution and a frequency variable may have a Poisson. For the avoidance of doubt we shall graph it as well.

When the variable type and distribution is known, the lookup tables below can be used to deduce which model is needed and which code can be used to do that. Stata code is shown for convenience, although SAS or R code would also suffice. See the Stata help documentation for more details

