### 3.2 Randomisation and Blinding

*See also the protocol section “Randomisation” and “Blinding and code-breaking”*

Participants will be randomised by the local research team intended to conduct randomisation through a minimisation module on REDCap.

There are two arms, one for the intervention, one for the control.

Eligible participants will be individually randomised with a 1:1 allocation ratio to receive either the intervention or the control through minimisation with a 20% random element. The two stratified variables will be performance status (“0” vs “1-2”) and age at diagnosis (“< 70 years” and “≥70 years”) with the threshold of 70 chosen as the median age of diagnosis of colorectal cancer.

Allocation concealment is achieved as randomisation occurs after the baseline visit, the randomisation algorithm is unmodifiable and concealed from investigators and the local research teams, and the local research teams have no access to the total number of participants randomised to each group.

It is impossible to blind the participants and research nurses due to the nature of the intervention. Therefore, procedures for breaking the allocation code are not applicable. However, the assessors of the future primary outcome (research nurses conducting the post-operative follow-up visit) will be blinded. The central study team (chief investigator and members of the trial management committee) will be blinded to the adverse events and all post-operative data by trial group. The trial statistician is not blinded.

Full details of the randomisation are available in the latest RBP (Randomisation and Blinding Plan), which is stored in the confidential statistical section of the TMF.

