### 4.2 Output variables

We expect to model all secondary outcome variables, except survival, recurrence, new primary/secondary cancer, re-admission rates, re-operation rates, costs and resource use, and adverse events. The final decision will depend on the available data. For example, if the counts for conversion to open surgery rates are very low, we will not model this outcome.

Therefore, we plan on analysing:

- Morbidity (five variables not including 2iii survival)
- Operative outcomes (seven variables not including re-operation and re-admission rates)
- Hospital stay (two variables)
- Anthropometry (two variables)
- Fitness (one variable)
- Health-related quality of life (HRQoL) (three variables)

That's twenty variables equating to at least 20 models, as some of those variables will be further subdivided (eg HRQoL variable "EQ-5D-5L" has two subdivisions, index and VAS).

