### 22.1 GLMs

| #  | Variable Type                 | Distribution                              | Link Fn   | Example Stata Code †††                      |
|----|-------------------------------|-------------------------------------------|-----------|--------------------------------------------------------|
| 1  | Continuous (Normal)           | Gaussian                                  | Identity  | glm depvar indepvars, family(gaussian) link(identity)  |
| 2  | Continuous (SPC) † | Inverse Gaussian                          | Power -2  | glm depvar indepvars, family(igaussian) link(power -2) |
| 3  | Binary                        | Binomial (multiple) or Bernoulli (single) | Logit     | glm depvar indepvars, family(binomial) link(logit)     |
| 4  | Count/Rate (Poisson)          | Poisson                                   | Log       | glm depvar indepvars, family(poisson) link(log)        |
| 5  | Count/Rate (NB)               | Negative binomial                         | Log       | glm depvar indepvars, family(nbinomial) link(log)      |
| 6  | Continuous (SPC) † | Gamma                                     | Power -1  | glm depvar indepvars, family(gamma) link(power -1)     |
| 6  | Continuous (Time)             | Gamma?                                    | Power -1? | glm depvar indepvars, family(gamma) link(power -1)     |
| 99 | Time-to-event                 | Exponential ††                 | Log       | glm depvar indepvars, family(exponential) link(log)    |

† SPC = Skewed positive continuous variable.

†† Not available in Stata. Code shown is synthetic. GLMs in this case would require another language

††† For a full list of families, link functions in Stata and their valid combinations, please see Stata help. Note that “inverse” is the same as “power -1”, “inverse squared” is the same as “power -2”, and so on

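### For weight and the other baseline-measured continuous outcomes, the supplement picks the model from the raw variable rather than from residuals given baseline, which can lead to a gamma inverse-link model with a less precise estimate

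*Combined protocol and SAP*

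**What the plan says.** The secondary-outcomes supplement, section 4.1, gives the model inputs as arm, baseline value, time point and the combined stratum, with participant as the random effect. Section 4.3 prefers GLMs wherever they can be used. Section 5 lists weight, fat-free mass, sit-to-stand time, EQ-5D-5L and HADS as continuous and leaves their distribution to the lookup.

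Section 22 describes the lookup in three steps:

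- Start from type: "The type of a variable can be used to deduce the variable distribution".
- Confirm by eye: "For the avoidance of doubt we shall graph it as well".
- Read off the model: "When the variable type and distribution is known, the lookup tables below can be used to deduce which model is needed".

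In section 22.1 a normal continuous variable goes to "glm depvar indepvars, family(gaussian) link(identity". A skewed positive one (footnote: "SPC = Skewed positive continuous variable") goes to inverse Gaussian with power -2 or to "glm depvar indepvars, family(gamma) link(power -1". The row for time measurements also names gamma with the inverse link, but prints both with question marks.

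Section 20.3, the only worked model for weight, is a linear mixed model with baseline, time point and stratum as fixed effects. On who does the choosing, SAP 3.2 says: "The trial statistician is not blinded".

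**The concern.** Sections 4.3 and 22 speak only of the distribution of the variable. They do not mention its distribution given the covariates in section 4.1, and they ask for no residual plot or fit check. A GLM's family and link describe the outcome conditional on those covariates.

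The two can differ sharply for weight. Entry at BMI 28 or above (25 or above for some ethnic groups; protocol 8.2) cuts the distribution off from below, so a right tail at follow-up is plausible. Most of that tail is already present at baseline, and what remains after adjustment can be symmetric. Type alone cannot settle the matter, because the normal and the skewed rows are both continuous; the graph of the raw variable has to decide.

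At stake is the precision of the comparison closest to the intervention's mechanism, and whether its 95% interval covers as stated.

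**Working it through.** The documents give no baseline weight SD and no standard error for the weight comparison, so there is no figure of the plan's own to reproduce. The baseline weight distributions below are assumptions.

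**Inputs.** 36 per arm (protocol 11.3). Mean loss 7% with SD 1.8 kg for this programme, and SD 4 to 5 kg for less intensive pre-operative programmes (protocol 5). I read each SD as the spread of weight change in kg. One follow-up time was simulated.

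**Models compared.**

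- Gaussian identity: E(Y) = a + t·arm + b·baseline + stratum.
- Gamma inverse: 1/E(Y) = a + t·arm + b·baseline + stratum. The effect in kg is the average difference in predictions with arm set to 1 and to 0, with a delta-method SE.

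**Hand check of the Gaussian SE.** SD × √(1/36 + 1/36) = 1.8 × 0.2357 = 0.42 kg, and 5 × 0.2357 = 1.18 kg. The simulated values below are slightly higher, as expected when a 7% proportional loss is fitted with one common slope.

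**Why the inverse link misfits.** Take untreated weight equal to baseline, at a height of 1.69 m and BMI of 28, 32.5 and 37 (28 plus 0, 4.5 and 9). A line on the 1/weight scale through the two ends gives 2 × 28 × 37/65 = 31.88 at the middle. That is 0.62 BMI units low, or 0.62 × 1.69² = 1.8 kg, as large as the residual SD. On the log scale the middle is √(28 × 37) = 32.19, or 0.9 kg low. The identity link has no error.

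**Simulation A** (800 data sets per row). Wide baseline: follow-up SD about 16.5 kg, skewness about 0.9. Median SE in kg; the last three columns are ratios to Gaussian identity.

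| Change SD (kg) | Gaussian identity SE | Gamma inverse SE | Gamma inverse | Gamma log | Gamma identity |
|---|---|---|---|---|---|
| 1.8 | 0.458 | 1.005 | 2.19 | 1.38 | 0.99 |
| 2.5 | 0.622 | 1.106 | 1.78 | 1.25 | 0.99 |
| 3 | 0.740 | 1.194 | 1.61 | 1.19 | 1.00 |
| 4 | 0.979 | 1.381 | 1.41 | 1.13 | 1.00 |
| 5 | 1.218 | 1.594 | 1.31 | 1.10 | 1.00 |

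Raw weight failed a skewness test in 71 to 78% of these data sets, while residual skewness was about 0. With a milder baseline (SD about 12 kg, skewness about 0.4) the gamma inverse ratio was 1.48 at SD 1.8 kg, 1.23 at 3, 1.15 at 4 and 1.12 at 5. The skewness test then failed in 24 to 32%.

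**Simulation B** (400 trials per setting). BMI = 28 + exponential with mean 3, 4.5 or 6.

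| Change SD (kg) | Gamma inverse SE ratio (mean 3, 4.5, 6) | 95% interval coverage |
|---|---|---|
| 1.8 | 1.64, 2.10, 2.68 | 95%, 90%, 91% |
| 3 | 1.32, 1.55, 1.98 | not recorded |
| 4.5 | 1.17, 1.32, 1.56 | 91 to 93% |

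At SD 1.8 kg, Gaussian coverage was 95 to 97%. The Monte Carlo error on 95% coverage is √(0.95 × 0.05/400) = 1.1 points, so 90% is a real shortfall.

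**How much baseline adjustment survives** (SD 1.8 kg, 300 trials per setting, the same three BMI tails). Unadjusted SE: 2.9, 3.8, 4.5 kg. Gamma inverse: 0.72, 0.98, 1.22. Gaussian: 0.44, 0.44, 0.46. Share of the SE reduction kept: (2.9 − 0.72)/(2.9 − 0.44) = 89%, (3.8 − 0.98)/(3.8 − 0.44) = 84%, (4.5 − 1.22)/(4.5 − 0.46) = 81%.

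**The case against.** The strongest reply is that the supplement does not commit weight to gamma. Section 20.3 models it with an identity link and baseline adjustment. The tables are offered as something that may be used, with example code. Section 22.2 allows ordinary regression where a GLM is inferior, and section 25 lists a log link for gamma. All of this is true, and it means the plan is ambiguous rather than fixed on a poor model. It does not remove the point: section 5 still sends weight to the lookup, nothing gives section 20.3 precedence, and no criterion for inferior is stated.

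Several stronger readings are tempting but not supported:

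- *Every outcome is affected.* Section 5 fixes binary outcomes as binomial and does not model the CR29 items. The EQ-5D-5L index can fall below 0 and HADS can equal 0, so the positive-skew rows do not fit them. The selection rule is wrong for them too, but the SE figures are for weight only.
- *The gamma family is the cause.* Gamma with identity link leaves the SE unchanged; the loss comes from the tabulated link. Gamma identity is still no remedy. It is not a tabulated row, it moved the median estimate from −6.71 to −6.41 kg in simulation A (wide baseline, SD 1.8 kg), and its coverage fell as low as 83%.
- *The standard error doubles.* That holds only with tight weight change and a wide baseline.
- *Baseline adjustment is lost.* Over 80% of its gain remains.
- *The test-failure rates are the chance of choosing gamma.* The plan uses a graph, not a test.
- *Section 4.2 leaves the family to the data.* Its sentence "The final decision will depend on the available data" concerns whether to model an outcome at all; its example is low conversion counts.
- *The statistician would choose with the arms in view.* SAP 3.2 leaves the statistician unblinded and section 22 does not ask for masked graphs, but neither says the choice would use arm.

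**Conclusion.** The selection step looks at the wrong distribution for the baseline-measured lookup outcomes, and the supplement disagrees with itself on weight. If raw weight is classed as skewed and the tabulated gamma row is used, the SE is about 1.1 to 2.7 times that of the Gaussian identity model. The high end belongs to SD 1.8 kg, the figure given for this programme. At 4 to 5 kg the ratio is about 1.1 to 1.6. Coverage drops to about 90% in several settings.

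These sizes rest on assumed baseline weights, normal errors, a linear relation with baseline and a single follow-up; a repeated-measures model was not simulated.

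A reader might infer a threat to the go/no-go decision. There is none. Adherence is judged on the proportion losing at least 5% of weight, SAP 3.7.1 keeps intervals out of the decision, and SAP 4.1 reports no p-values and treats intervals as nominal. The harm is wider or under-covering intervals for secondary outcomes.

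**What to change.** Amend sections 4.3, 5 and 22 of the supplement:

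1. For weight, fat-free mass, sit-to-stand, EQ-5D-5L and HADS, name a Gaussian identity model on arm, baseline and combined stratum. Where there are several follow-up times, make it a linear mixed model with time point and a participant random effect, as section 4.1 already provides.
2. Replace the lookup entry for these outcomes in section 5 and reconcile it with sections 20.3 and 22. The example should follow section 4.1, with arm fixed and participant random; as printed it puts the random intercept on arm.
3. Judge fit from the residuals of that model, not from the raw variable.
4. Show any other family as a sensitivity analysis, chosen on pooled data with arm masked.

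The cost is a wording change before database lock and slightly less flexibility for the analyst.
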